##### Upper-body flexibility

The *back scratch test*, a measure of overall shoulder range of motion, involves measuring the distance between (or overlap of) the middle fingers behind the back with a ruler [24]. The best score of two attempts for each arm in centimetres will be recorded and the average of both arms will be used in the analyses.

##### Motor agility/dynamic balance

The *timed up and go test* [27] will be performed to assess the dynamic balance. The participant will be seated in a chair with arms and trunk supported. The participant will be instructed to stand up on the word “go” and walk 3 meters in a straight line, turned 180°, walk back to the chair and sit down again in the chair. One familiarization trial will be undertaken. After 1-min rest, the test will be performed twice separated by 1-min. The time from the start until the participant sit down in the chair with back support will be measured and the best of the 2 attempts will be used.

##### Self-perceived physical fitness

The *International Fitness Scale* [28] consists of five Likert scale questions asking how participants perceive their overall fitness, cardio-respiratory fitness, muscular strength, speed-agility and flexibility (“very poor”, “poor”, “average”, “good” and “very good”) in comparison with their friends.

#### Physical activity and sedentary behaviour

*Accelerometry* will be used to objectively assess physical activity and sedentary time. Women will be asked to wear a tri-axial accelerometer (GT3X+, Pensacola, Florida, USA) for 9 consecutive days, starting the same day they receive the monitor (e.g. participants who receive the accelerometer on Monday, will carry the device until Tuesday of the next week). The first and last day will be excluded from the analyses, accounting for a total of 7 days of registering. Participants will be instructed to wear the accelerometer during the whole day (24 h) on their lower back attached by an elastic belt. To prevent any damage to the devices, these will be taken off during water-based activities such as bathing or swimming. Time engaged in light, moderate, and moderate-vigorous intensity physical activity and sedentary time will be calculated.

The *Sedentary Behaviour Questionnaire* [29, 30] assesses the amount of time spent doing 11 behaviours. The 11 items will be completed separately for weekday and weekend. Response options are none, 15 min or less, 30 min, 1 h, 2 h, 3 h, 4 h, 5 h, or 6 h or more. The time spent on each behaviour will be converted into hours (e.g., a response of 15 min will be recorded as 0.25 h). For the total scores of sedentary behaviour, hours per day for each item will be summed separately for weekday and weekend. To obtain weekly estimates, weekday hours will be multiplied by 5 and weekend hours will be multiplied by 2 and these will be summed for total hours/week.

The short version of the *ALPHA Environmental questionnaire* [31] will be used to assess environmental perceptions about physical activity. The questionnaire will provide information about types of residences in the neighbourhood, distances to local facilities, walking or cycle infrastructure in the neighbourhood, cycling and walking network, neighbourhood safety, home and work/study environment mode of active travel.

#### Sleep quality

The *Pittsburgh Sleep Quality Index* [32] will be used to assess sleep quality and disturbances over a l-month time interval. Nineteen individual items generate seven “component” scores: subjective sleep quality, sleep latency, sleep duration, habitual sleep efficiency, sleep disturbances, use of sleeping medication, and daytime dysfunction. Each component yields a score ranging from 0 to 3, with 3 indicating the greatest dysfunction. The seven component scores are summed to provide a global sleep quality score (range 0 to 21) with higher scores indicating poorer sleep quality.

#### Quality of life, mental health and positive health

We will determine participants’ quality of life with the *Short-Form Health Survey 36* (SF-36) [33]. The SF-36 is a generic instrument for assessing health-related quality of life. It contains 36 items grouped into 8 dimensions: physical functioning, physical role, body pain, general health, vitality, social functioning, emotional role, and mental health. The scores range from 0 to 100 in every dimension, where higher scores indicate better health.

The *EQ-5D-5 L* consists of two parts. The first will be used to assess 5 dimensions of health related quality of life: mobility, self-care, usual activities, pain/discomfort and anxiety/depression, each of which is defined through five severity levels [34, 35]. The instrument therefore defines 3125 different health states from all the possible combinations of dimensions and levels of severity. EQ-5D-5 L health states may be converted into a single index value [34, 35]. This index ranges from 1 (best health status) to 0 (death). The second part consists of a 20-cm, vertical visual analogue scale (VAS), in the form of a thermometer, with endpoints of worst and best imaginable health status (scored 0 and 100, respectively) [34, 35]. This questionnaire will be administered at 3 different time points: at the beginning of the study, at 8 weeks and at 16 weeks, moreover it will be used to perform the cost-utility analysis.

The *Rosenberg Self-Esteem Scale* [36] is a 10-item scale to analyse the global self-esteem [37]. Each item is rated on a 4-point Likert scale, ranging from 1 = “strongly disagree” to 4 = “strongly agree”. The score ranges from 10 to 40, and higher scores reflect greater self-esteem.

The *brief COPE* [38, 39] is a 28-item scale that assesses coping strategies. Participants will be asked to rate how often they use specific coping strategies on a 4-point Likert scale, from 0 = “I haven’t been doing this at all” to 3 = “I’ve been doing this a lot”. The 28 items are paired together describing 14 different coping strategies: active coping, planning, positive reframing, acceptance, humour, religion, use of emotional support, use of instrumental support, self-distraction, denial, venting, substance use, behavioural disengagement and self-blame. Score for each subscale ranges from 0 to 6, and higher score indicates more frequency of the particular coping strategy.

The *General Self-efficacy Scale* [40, 41] is a 10-item scale to analyze the global self-efficacy. Each item is rated on a 4-point Likert scale, ranging from 1 = “not all true“ to 4 = “exactly true”. The score ranges from 10 to 40 where higher scores reflect greater general self-efficacy.

The *Beck Depression Inventory-II* [42, 43] will be used to assess depression severity. It contains 21 items measuring depressive symptoms such as sadness, pessimism, suicidal thoughts or wishes, tiredness or fatigue, loss of energy, and loss of pleasure, among others. Each item is scored on a scale ranging from 0 to 3. The global score ranges from 0 to 63 with higher score indicating greater degree of depression. A score of ≤13, 14–19, 20–28, and ≥29 represents minimal, mild, moderate, and severe depressive symptoms, respectively

The *State Trait Anxiety Inventory* [44] consists of 2 scales for measuring state anxiety and trait anxiety. Each scale comprises 20 items with scores ranging from 1 to 4. The total score of each scale ranges from 20 to 80 and higher values indicate higher levels of anxiety.

Positive health will be assessed by means of the following questionnaires:The *Trait Meta-Mood Scale* [45] is comprised of 3 subscales to assess emotional attention, emotional clarity and emotional repair. Each subscale comprises 8 items. Participants rate their responses using a 5-point Likert scale, with 1 = “strongly disagree” to 5 = “strongly agree”. The subscales score range from 8 to 40 and higher scores reflect greater emotional attention, clarity, and repair.The *Positive and Negative Affect Schedule* [46, 47] is a 20-item questionnaire designed to measure positive and negative affect. The questionnaire includes 10 positive and 10 negative emotional states that should be answered on a 5-point Likert scale, from 1 = “very slightly or not at all” to 5 = “extremely”. The score ranges from 10 to 50 for both subscales (positive affect and negative affect), and higher scores reflect greater affective well-being.The *Satisfaction with Life Scale* [48, 49] assesses the perceived global life satisfaction. It consists of 5 items with a 5-point Likert scale from 1 = “strongly disagree” to 5 = “strongly agree”. The score ranges from 5 to 25, and higher scores reflect greater life satisfaction.The *Life Orientation Test Revised* [50, 51] is a 10-item scale that assesses participants’ expectations about their future and their general sense of optimism. Six items (three reverse-scored) are used to obtain the total optimism score. Each item is rated on a 5-point Likert scale ranging from 0 (“strongly disagree”) to 4 (“strongly agree”). The total score ranges from 0 to 24, with higher scores indicating higher levels of optimism. The remaining 4 items are filler questions.The *Subjective Happiness Scale* [52, 53] is a 4-item scale that assesses the global subjective happiness. Each item is rated on a 7-point Likert scale (e.g., “In general, I consider myself”, from 1 = “Not a very happy person” to 7 = “A very happy person”). The total score is the mean of all the four items, ranging from 1 to 7, and higher score indicates greater subjective happiness.The *10-item Connor-Davidson Resilience Scale* [54, 55] assesses resilience to stress, which is a construct refering to a dynamic process of positive adaptation to adverse changes in life circumstances [56, 57]. Each item ranges from 0 = “not true at all” to 4 = “true nearly all the time”. The total score range from 0 to 40, and higher scores indicate greater resilience.

#### Menopause symptoms

The *Blatt-Kupperman menopausal index* [58] consists of 11 items including sweating/hot flushes, palpitation, vertigo, headache, paraesthesia, formication, arthralgia, and myalgia (categorized as somatic symptoms), and fatigue, nervousness, and melancholia categorized as psychological symptoms. A scale ranging from 0 to 3 points is used to describe the severity of the complaints. The total score ranges from 0 to 63, calculated as the sum of all items by the weighting factor. Scores ranging from 0–6, 7–15, 16–30, and 30 are used to rate the degree of severity as none, mild, moderate, and severe, respectively.

The *Cervantes scale* [59] is a health-related quality of life questionnaire specific for the menopause. The scale has 31 items and covers 4 domains: menopause and health (15 items), psychological domain (9 items), sexuality (4 items), and couple relationship (3 items). Each item score ranging from 0 to 5. The global score range from 0 to 155 (from better to worse quality of life).

### Measurements procedures

The women will be cited three days to complete all the measurement protocol. The first day, participants will attend the primary care centre and complete the following assessments in the same order as presented here: socio-demographic and clinical information, blood pressure and resting heart rate, body composition and physical fitness. The participant will then receive the accelerometer and all the questionnaires to be completed at home and will be cited eight days later to return them. Additionally, the primary care centre will cite participants another day for the biochemical analysis.

### Statistical analysis

Baseline characteristics of the study participants will be presented as mean (standard deviation) for continuous variables and proportions for categorical variables.

Statistical analysis will be performed on the intention to treat population, thus including all randomized participants (in the groups to which they were randomly assigned) in the analysis. Missing data will be replaced using multiple imputations. The effects of the intervention on the primary and secondary outcomes will be assessed with repeated measures analysis of covariance adjusted for age and baseline values. The effect size (95 % confidence interval) and statistical significance will be reported for each study outcome with regards to the main group (between-subjects) time (within-subjects) and their interaction (group × time) effects. The statistical significance will be set at the conventional level of p<0.05. To account for potential estimations biases or inefficiency, sensitivity analyses will be undertaken using baseline observation carried forward imputation, and also the available case population (participants who actually received the treatment; i.e. no imputations).

*Ancillary analyses.* "Per-protocol" analyses will also be performed on participants with overall ≥75 % treatment compliance.

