**Methods/Design:**

The present study is a Randomized Controlled Trial.

A total of 150 eligible women will be recruited and randomly assigned to either a 16-week exercise intervention (3 sessions/week), or to usual care (control) group.

The primary outcome measure is the incremental cost-effectiveness ratio. The secondary outcome measures are: i) socio-demographic and clinical information; ii) body composition; iii) dietary patterns; iv) glycaemic and lipid profile; v) physical fitness; vi) physical activity and sedentary behaviour; vii) sleep quality; viii) quality of life, mental health and positive health; ix) menopause symptoms. All outcomes will be assessed at baseline and post intervention. The data will be analysed on an intention-to-treat basis and per protocol. In addition, we will conduct a cost effectiveness analysis from a health system perspective.

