### Sample size

The number of participants to be included in the study was calculated on the basis of the change in quality of life as assessed with the *EuroQol 5D (*EQ-5D-5 L). To the best of our knowledge, there is no available data regarding group differences in changes in quality of life following any type of intervention in middle aged women. Therefore, we assumed a difference of 0.07 units as clinically meaningful based on previous observations from our group (unpublished observations). Therefore, a total of 124 participants (62 per group) is needed to detect a mean group difference of 0.07 and a standard deviation of 0.12 in the total EQ-5D score with a power of 90 % and α of 0.05. However, we will attempt to exceed this sample size to allow for withdrawals. Assuming a maximum lost-to-follow up of 20 %, a minimum of 75 participants per group will be recruited (*n* = 150).

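### For outcomes measured only twice, the repeated-measures ANCOVA uses baseline as both covariate and time level, so its group main effect is half the adjusted post-intervention difference

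*Protocol article*

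**What the plan says.** The Statistical analysis section of the protocol article fixes both the model and its output. Intervention effects "on the primary and secondary outcomes will be assessed with repeated measures analysis of covariance adjusted for age and baseline values". For each study outcome, effect size, 95 % confidence interval and significance are to be given "with regards to the main group (between-subjects) time (within-subjects) and their interaction (group × time) effects".

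The visit schedule comes from two places. The Methods/Design part of the abstract states: "All outcomes will be assessed at baseline and post intervention". The section on quality of life, mental health and positive health adds one exception: the EQ-5D-5L is administered "at 3 different time points: at the beginning of the study, at 8 weeks and at 16 weeks".

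The article does not say outright whether baseline is a level of the time factor.

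**The concern.** For an outcome with two visits, the specification leaves two readings.

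- **Baseline is a covariate only.** One response per woman remains. The promised time and group × time effects then cannot be estimated.
- **Baseline is a level of time.** The model can be fitted, but it adjusts for a variable that is also one of its responses. Given baseline, the group difference at the baseline level is zero by construction, and the group main effect averages that zero with the real difference.

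Only the second reading yields the promised output. The line labelled as the group effect would then understate the intervention effect by half, with a confidence interval that is too narrow by the same factor and centred on the wrong value. This would apply to every two-visit outcome, such as body composition, lipid profile, fitness, sleep and menopause symptoms. A reader who takes the group line as the treatment effect would be misled about size, although not about significance.

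**Working it through.** **Inputs.** From Sample size: "needed to detect a mean group difference of 0.07 and a standard deviation of 0.12 in the total EQ-5D score"; that section sets 90 % power at α = 0.05 and arrives at 62 per group. From Statistical analysis: covariates are baseline and age. The correlation between visits is not given; 0.3, 0.5 and 0.7 are assumed. The SD of 0.12 is applied at each visit for illustration.

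**1. The plan's own figure.** n per group = 2 × (1.96 + 1.2816)² × (0.12/0.07)² = 2 × 10.51 × 2.939 = 61.8, so 62 per group and 124 in total. This agrees with the plan at two-sided α = 0.05; power at 62 per group is 90.1 %.

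**2. Two visits, algebra.** Let the ordinary ANCOVA be

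Y1 = a + τ·group + β·Y0 + γ·age + e.

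- Group main effect (mean of the two visits): (Y0 + Y1)/2 = a/2 + (τ/2)·group + ((1 + β)/2)·Y0 + (γ/2)·age + e/2. The group coefficient is τ/2.
- Group × time (difference of the two visits, with the covariates allowed a separate slope at each visit): Y1 − Y0 = a + τ·group + (β − 1)·Y0 + γ·age + e. The group coefficient is τ.

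The residuals are the same up to a factor of 2, so the t statistics are identical. If the covariates are instead given one common slope over visits, the group line is still τ/2. Group × time then becomes the unadjusted difference in change, which still estimates τ under randomization but no longer has the same p-value as the group line.

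**3. Two visits, simulation.** 4,000 trials, 62 per group, SD 0.12, true difference 0.07, separate slopes:

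| Correlation | Group main effect | Group × time | ANCOVA of post value | Rejection rate, all three |
|---|---|---|---|---|
| 0.3 | 0.0349 | 0.0698 | 0.0698 | 92.1 % |
| 0.5 | 0.0349 | 0.0698 | 0.0698 | 95.9 % |
| 0.7 | 0.0351 | 0.0702 | 0.0702 | 99.5 % |

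The ratio is 0.50 throughout and does not depend on the correlation.

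**4. What the interval would look like.** At correlation 0.5, the standard error of the adjusted difference is 0.12 × √(1 − 0.5²) × √(2/62) = 0.0187. With an estimate of 0.07, the 95 % interval is 0.07 ± 1.98 × 0.0187, about 0.033 to 0.107. The group line would print 0.035 with an interval of about 0.017 to 0.053, which excludes 0.07. Even at correlation 0, its upper limit is 0.035 + 1.98 × 0.12 × √(2/62)/2, about 0.056.

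**5. EQ-5D-5L, three visits.** If baseline is a time level, the group main effect is (0 + d8 + d16)/3. If time is weeks 8 and 16 only, it is (d8 + d16)/2. The week-8 effect is not in the article, so three trajectories are assumed, with d16 = 0.07:

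| Week-8 effect | Baseline as a time level | Weeks 8 and 16 only |
|---|---|---|
| 0.07 (full by week 8) | 0.047 (2/3 of d16) | 0.070 |
| 0.035 (linear) | 0.035 (1/2) | 0.0525 |
| 0 (week 16 only) | 0.023 (1/3) | 0.035 |

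In the last column, any shortfall from 0.07 comes from averaging two follow-up visits, not from baseline.

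**The case against.** The strongest reply is that the planned output already contains the right answer. With two visits, group × time carries the full effect, and its interval is also promised. With separate covariate slopes, its p-value equals that of the group line. Type I error and power are untouched. This stands, and it limits the point to one of three reported lines. That line is nevertheless the one labelled as the group effect.

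Second, the effect size is not defined. The halving applies to a raw mean difference. Partial eta-squared, or a difference standardised by its own residual SD, would be the same for both lines when the t statistics are identical. This also stands.

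Third, an article may leave the choice of contrast to the analysis plan. That is fair for silence on which line is the treatment effect, and no fault is claimed for that silence. It does not cover a stated model whose stated output, for two-visit outcomes, is either impossible or obtained by using baseline twice.

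A reader might go further and infer that every reported treatment effect is halved, including the EQ-5D-5L effect behind the sample size, and even the primary result. The article does not support this:

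- For the EQ-5D-5L, weeks 8 and 16 as responses with baseline and age as covariates also fits the wording, and then baseline dilutes nothing.
- The Sample size section names no time point, so a week-16 contrast there is an inference.
- The incremental cost-effectiveness ratio is built from group mean costs and QALYs and has its own bootstrap analysis. It has no baseline value, so the halving cannot reach it.

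**Conclusion.** The point holds for outcomes measured only at baseline and after the intervention. The specification as written either cannot deliver the time and group × time effects or uses baseline as both response and covariate. In the second case the raw group main effect and its interval are exactly half the adjusted post-intervention difference (0.035 for a true 0.07), whatever the correlation. The double use is deduced from the visit schedule and the promised output; the article does not state it.

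This is a fault of estimate and labelling. Power is not lost, and the group and group × time p-values coincide where the covariates act separately on each visit. For the EQ-5D-5L the dilution is conditional: 1/3 to 2/3 of the week-16 effect over the assumed trajectories if baseline is a time level, and none from baseline if it is not. The primary outcome is outside the point.

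**What to change.** For two-visit outcomes, replace the repeated-measures model by ANCOVA of the post-intervention value on group, baseline value and age. Report one adjusted between-group difference with its 95 % confidence interval in place of the group, time and group × time lines.

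For the EQ-5D-5L, state that weeks 8 and 16 are the only response visits, keep baseline and age as covariates, and report the week-16 group difference as the treatment effect.

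The cost is a change of analysis wording before the data are analysed. No data, visits or participants are added. For two-visit outcomes no power is lost, because the ANCOVA test is the one that the group line already performs.

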### Interventions

The participants randomly assigned to the usual care (control) group will receive general advices from primary care centre medical staff about the positive effects of physical activity. The researchers will give 4 conferences (1 per month) explaining the benefits of exercise for longevity, prevention and treatment of diseases, the benefits of the Mediterranean diet, nutritional education, ergonomic advises, exercise to perform at home (e.g. stretching, strength training) and strategies to increase their daily physical activity levels.

The exercise intervention will be performed in four groups so that each group will comprise 15–20 participants. The groups will train 3 days/week (60 min per session) for a 16-week period at the primary care centre of Granada. The exercise intervention will meet the training standards of the American College of Sports Medicine [17] for adults. The exercise sessions will be designed, carefully supervised, guided and instructed by qualified exercise professionals.

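### The available-case sensitivity set is defined both by receipt of treatment and by absence of imputation, which are different sets; the per-protocol set is also selected after randomization and has no stated criterion for controls

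*Protocol article*

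**What the plan says.** All of this is in the protocol article.

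- **Main analysis (Statistical analysis):** "Statistical analysis will be performed on the intention to treat population, thus including all randomized participants (in the groups to which they were randomly assigned". Missing values are handled as follows: "Missing data will be replaced using multiple imputations". The model adjusts for age and baseline values.
- **Sensitivity analyses (same section):** one carries the baseline observation forward. The other uses "the available case population (participants who actually received the treatment; i.e. no imputations". Their stated aim is to address possible bias or inefficiency in estimation.
- **Ancillary analysis (same section):** per-protocol "analyses will also be performed on participants with overall" compliance of at least 75 %. No arm is named.
- **Abstract, Methods/Design:** "The data will be analysed on an intention-to-treat basis and per protocol".
- **Interventions, exercise arm:** "The groups will train 3 days/week (60 min per session) for a 16-week period".
- **Interventions, control arm:** the "usual care (control) group will receive general advices from primary care centre medical staff", plus four monthly conferences given by the researchers. The adherence strategies described (music, individual attention in sessions, calls after non-attendance) are built around the exercise programme.

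**The concern.** An available-case analysis normally keeps every randomized woman whose outcome was observed, in her assigned group. Its value here lies in the contrast with multiple imputation: same women as randomized, but no filled-in values. If the set is restricted to women who received the treatment, a second change comes in. Observed outcomes of non-attenders are discarded, and any departure from the main result may reflect that selection and not the imputation. The check then cannot be interpreted.

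The per-protocol set raises the related issue that compliance is post-randomization behaviour. Women who attend most of a 16-week programme may differ in health and motivation from those who do not. The retained exercise group is then not comparable with controls by virtue of randomization. The Abstract names the per-protocol analysis beside intention to treat without marking this difference in standing.

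**Working it through.** **1. The two halves of the definition, side by side.** Take four kinds of woman in the exercise arm:

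| Attendance | Outcome at follow-up | Kept if the rule is receipt of treatment | Kept if the rule is no imputation |
|---|---|---|---|
| Attended | Observed | Yes | Yes |
| Attended | Missing | Yes | No |
| Never attended | Observed | No | Yes |
| Never attended | Missing | No | No |

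The rules disagree in the second and third rows, so the plan's "the available case population (participants who actually received the treatment; i.e. no imputations" does not identify one set. Applying both conditions together keeps only the first row, which still drops observed outcomes in the third.

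**2. On whom the receipt or compliance filter falls.** The exercise programme has 3 × 16 = 48 sessions, and 75 % of these is 0.75 × 48 = 36. The only countable control component is the four conferences, of which 75 % is 3. The article does not say that conference attendance counts as compliance. As written, exclusions fall wholly or mainly on the exercise arm. Even if conferences counted, 3 of 4 talks is not a comparable hurdle to 36 of 48 supervised sessions.

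**3. Scale for judging size.** The plan's sample size uses a difference of 0.07, an SD of 0.12, 90 % power and α 0.05. With a two-sided test, n per group = 2 × (1.960 + 1.282)² × 0.12² / 0.07² = 61.8, so 62, as stated (power 0.901).

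**4. Illustrations of bias.** None of the adherence inputs is in the document.

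(a) Suppose a share p of the exercise arm is removed, those women would score g lower whatever their treatment, and all controls are kept. Bias = p × g.
- p = 0.25, g = 0.05: 0.25 × 0.05 = 0.0125, which is 0.0125 / 0.07 = 18 % of the target.
- p from 0.20 to 0.40, g from 0.03 to 0.08: from 0.20 × 0.03 = 0.006 to 0.40 × 0.08 = 0.032, or 9 % to 46 %.

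(b) The planned model adjusts for baseline. If g is a stable difference already present at baseline, and the assumed baseline slope is 0.5 to 0.7, the residual gap is 0.05 × (1 − 0.5) = 0.025 down to 0.05 × (1 − 0.7) = 0.015. With p = 0.25 the bias is 0.006 down to 0.004, or 9 % down to 5 % of 0.07.

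(c) Assume no true effect and 75 controls, all kept. Keep the top share k of 75 exercise women on a latent adherence variable that has correlation ρ with the outcome. Bias b = ρ × 0.12 × φ(c)/k, where c cuts off the upper share k. Type I error = Φ(b/SE − 1.96) + Φ(−b/SE − 1.96), with SE = 0.12 × √(1/75 + 1/(75k)).

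| k | ρ | b | Two-sided type I error |
|---|---|---|---|
| 0.8 | 0.1 | 0.004 | 0.055 |
| 0.8 | 0.5 | 0.021 | 0.173 |
| 0.6 | 0.1 | 0.008 | 0.063 |
| 0.6 | 0.5 | 0.039 | 0.40 |

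With ρ = 0 there is no bias. After covariate adjustment ρ must be read as the residual correlation. If controls are excluded by a comparable rule, the bias changes and may partly cancel.

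**5. A complier-average estimate as an alternative.** Using randomized arm as the instrument for at least 75 % attendance assumes that assignment does nothing for women below the cut. Suppose the full effect is 0.07, 25 % fall below the cut, and they gain half. The intention-to-treat effect is 0.75 × 0.07 + 0.25 × 0.035 = 0.06125. Dividing by 0.75 gives 0.0817, about 17 % above 0.07.

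**The case against.** The strongest reply is that the parenthesis is loose wording. It ends by ruling out imputation, follows the sentence on multiple imputation and stands beside baseline observation carried forward, so an observed-data set may be all that is meant. That reading is plausible, and under it women can be absent from either arm. It does not rescue the text, because the receipt condition is stated first and an analyst could follow it.

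A reader might go further and infer that only exercise women can fail either filter. The article does not support that. The 75 % rule names no arm, controls have conferences they could miss, and their compliance is undefined rather than impossible to fail. How compliance is counted in each arm may properly be left to a fuller document, so that silence alone is not a fault.

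A reader might also infer that the trial's main conclusion is biased. It is not: the main analysis keeps all randomized women as assigned, the per-protocol analysis is already labelled ancillary, and nothing lets either set override the main result. Nor does the plan reclassify women by treatment received, so calling the available-case set as-treated would be inaccurate.

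Finally, the bias figures depend on assumed inputs, and baseline adjustment may shrink them considerably. That objection stands in full.

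**Conclusion.** The available-case definition joins two different sets. Its receipt-of-treatment half, followed literally, confounds a check whose position in the plan and no-imputation gloss show it to be about missing data. That should be corrected. The per-protocol comparison is likewise selected after randomization, with no control-arm criterion stated, and can serve only as non-randomized supportive evidence.

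No bias size can be derived from the document. The illustrations run from zero (adherence unrelated to the adjusted outcome) to about 0.04 EQ-5D units (40 % removed, correlation 0.5, every control kept). They show what is possible and predict nothing. The consequence is confined to sensitivity and ancillary results.

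**What to change.** 1. Replace the parenthesis in Statistical analysis with a definition such as: all randomized participants with the outcome observed at follow-up, analysed in the assigned group regardless of treatment received, without imputation.
2. State the per-protocol compliance criterion for each arm, and describe the result as non-randomized supportive evidence wherever it is reported, including beside the intention-to-treat result in an abstract.
3. Optional: add a complier-average estimate by two-stage least squares, adjusted for age and baseline, with the explicit assumption that attendance below 75 % has no effect. Partial attenders would plausibly violate it, so this is a trade-off and not a correction.

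Items 1 and 2 cost two sentences and need no new data. Item 3 costs one extra model and gives a wider confidence interval than the simple per-protocol comparison.
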